### Visits at Three to Six Months, Twelve Months, and Twenty-Four Months

These visits can be performed in the clinic or via telephone; however, an in-person visit is preferred. Participants will be evaluated for updates and an assessment of the management plan, and for ADRs (if medication was prescribed at the previous visit). Also, patient questionnaires (EQ-5D-5L, UFS-QOL, and AMSS) will be administered. Follow up will occur after the baseline meeting at 3 to 6 months, 12 months, and 24 months.

### Preoperative Visit

This visit will only occur if the patient and physician agree on a procedural intervention. During this visit, participants will be evaluated for updates and an assessment of the management plan, and for ADRs (if medication was prescribed at the previous visit). Also, patient questionnaires (EQ-5D-5L, UFS-QOL, and AMSS) will be administered.

### Intraoperative Visit

This visit will only occur if the patient and physician agree on a procedural intervention. During this visit, information on the procedure performed and the AEs will be obtained. Specific details on the type of procedure, route, and surgical times will be recorded. Intraoperative description of outcomes, including morcellation (if performed), will be documented. In the case of myomectomy, fibroid cleavage planes and density (subjective) of the fibroids will be obtained as well.

### Postoperative Visit

This visit will only occur if the patient and physician agree on a procedural intervention. During this visit, information on AEs following the procedure, pathology, and patient questionnaires (EQ-5D-5L, UFS-QOL, and AMSS) will be recorded.

### Hysterectomy Postoperative Follow Up

If a patient undergoes a hysterectomy, a follow-up visit will occur 1 year after the hysterectomy (in addition to the postoperative visit). This follow up will replace all remaining scheduled follow-up study visits. Information on postoperative symptoms, overall satisfaction, UFS-QOL-Hysterectomy, and EQ-5D-5L will be obtained. Once this follow up is completed, the patient will be deemed to have completed all study visits.

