Treatment options for UF patients should ideally address 3 goals: (1) relief of signs and symptoms, (2) sustained reduction in fibroid size, and (3) retention or enhancement of fertility if desired. At the same time, treatment should also aim to improve quality of life, minimize side effects, be convenient for patients, and target UF directly [10]. Medical, procedural, or combined treatment options are available for patients with symptomatic UF. However, there were no medications to treat these women in Canada until 2013 when ulipristal acetate (UPA) was approved.

UPA has shown to be more effective than placebo [11] and as effective as the injectable gonadotropin-releasing hormone agonist leuprolide acetate [12] for treating UF symptoms. Leuprolide acetate received Health Canada indication for preoperative improvement of anemia in symptomatic UF women in 2017 [13]. The uptake, long-term clinical and patient-reported outcomes, efficacy, safety, as well as the pharmacoeconomics of indicated and off-label treatment options for these patients in Canada, have yet to be determined.

In the past 15 years, there has been only 1 completed registry for patients with UF who have undergone uterine artery embolization [14]. In the United States, the COMPARE-UF trial is underway [15]. A Canadian prospective patient registry provides the opportunity to address many unanswered questions, particularly the management patterns and outcomes associated with different treatments for UF and patients’ preferences for, and satisfaction with, managing UF symptoms.

With this background in mind, the objectives of this study are to (1) enhance the understanding of the natural history of symptomatic UF, (2) understand Canadian provider and patient preferences for managing symptomatic UF, (3) examine factors that have an impact on the uptake of UF treatment options and compliance with therapy, (4) examine the effectiveness and efficiency of UF treatment options across ethnicities in real-world practice in Canada, and (5) provide real-world data characterizing long-term clinical and patient-reported outcomes, including effectiveness and safety, associated with different UF management options.

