## Methods

### Overall Study Design and Plan

The CAnadian women wiTh Uterine fibroids REgistry (CAPTURE) is a prospective, observational cohort study (NCT02580578) that will include women who have been diagnosed with symptomatic UF. Outcomes will be evaluated as part of routine clinical practice. The target study population will include patients with a diagnosis of UF from 20 study sites across Canada. Participating physicians will not be required to perform any medical procedure that is outside their normal clinical practice. Serious and nonserious adverse drug reactions (ADRs) will be followed up as per local standard of care and as expected in an observational research study. Similarly, both serious and nonserious adverse events (AEs) during and following procedural intervention will be reported. Each study site was responsible for local ethics review board approval as per their institutional policy.

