### Baseline Visit

The baseline visit will involve (1) obtaining informed consent, (2) checking for inclusion/exclusion criteria, (3) collecting demographic information, (4) obtaining a medical history, and (5) assessing patient current health status. This will be followed by patient assessments that involve questions on UFs using the EuroQol 5-Dimensions 5-Levels (EQ-5D-5L) survey, the Uterine Fibroid Symptom and Quality of Life (UFS-QOL) questionnaire, the Aberdeen Menorrhagia Severity Scale (AMSS) questionnaire, and evaluation for concomitant medications and history of previous procedural interventions.

The EQ-5D-5L [16] is a validated 5-question survey with a visual analog scale used to measure health outcomes that provides a simple descriptive profile and a single index value for health status. The UFS-QOL [17] is a validated 37-question disease-specific symptom and health-related quality of life questionnaire for UF. It has been used extensively in studies to assess the impact of the disease in patients and treatment options in randomized clinical trials. The AMSS questionnaire is a validated 15-question survey that evaluates the severity and effect of bleeding that occurs during and between menses. There are 7 baseline questions for UF patients asking about the purpose of their visit and what outcome they are hoping to achieve.

If deemed eligible for registry participation, the patient will return for a visit in 3 to 6 months. When available, imaging and other test results (biopsies, blood work) will also be documented.

**Table 1 table1:** Schedule of events of the CAPTURE study at baseline and scheduled visits.

Examinations	Scheduled follow-up visits			
	Baseline	3- to 6-month^a^	12-month^a^	24-month^a^
Signed informed consent form^b^	✓	—	—	—
Inclusion/exclusion criteria	✓	—	—	—
Demographics	✓	—	—	—
Medical history	✓	—	—	—
Fertility wishes	✓	✓	✓	✓
Blood work (hemoglobin)^c^	✓	✓	✓	✓
Gynecologic symptoms	✓	✓	✓	✓
Ultrasound of fibroids	✓	✓	✓	✓
Type and location of fibroids	✓	—	—	—
Endometrial biopsy^c^	✓	—	—	—
Planned/updated management plan	✓	✓	✓	✓
UFS-QOL^d^	✓	✓	✓	✓
Bleeding assessment^e^	✓	✓	✓	✓
EQ-5D-5L^f^	✓	✓	✓	✓
Concomitant medications	✓	✓	✓	✓
Adverse events	—	✓	✓	✓

^a^Visits can be performed by telephone or in clinic; however, an in-person visit is preferred.

^b^Must be obtained from patient prior to study enrollment.

^c^To be captured if available.

^d^UFS-QOL: Uterine Fibroid Symptom and Quality of Life questionnaire.

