^e^Tool for assessment is the Aberdeen Menorrhagia Severity Scale questionnaire.

^f^EQ-5D-5L: EuroQol 5-dimensions 5-levels survey used to measure health status.

**Table 2 table2:** Schedule of events of the CAPTURE study at procedural intervention and hysterectomy.

Examinations	Procedural intervention^a^			Hysterectomy
	Preoperative	Intraoperative	Postoperative	1-year follow up
Signed informed consent form	—	—	—	—
Inclusion/exclusion criteria	—	—	—	—
Demographics	—	—	—	—
Medical history	—	—	—	—
Fertility wishes	—	—	—	—
Blood work (hemoglobin)^b^	✓	—	—	—
Gynecologic symptoms	—	—	—	✓
Ultrasound of fibroids	✓	—	—	—
Type and location of fibroids	—	—	—	—
Endometrial biopsy	—	—	✓	—
Planned/updated management plan	✓	—	—	—
UFS-QOL^c^	✓	—	✓	✓
Bleeding assessment^d^	✓	—	✓	—
EQ-5D-5L^e^	✓	—	✓	✓
Concomitant medications	✓	—	—	—
Adverse event	✓	✓	✓	—

^a^Procedural intervention is not mandatory in the registry, and data will be collected if physician and patient decide on a procedural intervention to address symptoms associated with uterine fibroids.

^b^To be captured if available.

^c^UFS-QOL: Uterine Fibroid Symptom and Quality of Life questionnaire.

^d^Not required if patient undergoes hysterectomy procedure. Otherwise the tool for assessment is the Aberdeen Menorrhagia Severity Scale questionnaire.

^e^EQ-5D-5L: EuroQol 5-dimensions 5-levels survey used to measure health status.

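### After hysterectomy, no scheduled visit beyond the postoperative visit asks about adverse events, although long-term safety of different management options is an objective

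*Protocol article*

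**What the plan says.** All references are to the Protocol article.

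- **Objective.** The fifth objective, at the end of the Introduction, is to "provide real-world data characterizing long-term clinical and patient-reported outcomes, including effectiveness and safety, associated with different UF management options".
- **Hysterectomy visit, text.** The section Hysterectomy Postoperative Follow Up adds one visit a year after surgery. Its content: "Information on postoperative symptoms, overall satisfaction, UFS-QOL-Hysterectomy, and EQ-5D-5L will be obtained". Its effect on the schedule: "This follow up will replace all remaining scheduled follow-up study visits". Then: "Once this follow up is completed, the patient will be deemed to have completed all study visits".
- **Hysterectomy visit, table.** In Table 2 ("Schedule of events of the CAPTURE study at procedural intervention and hysterectomy"), the adverse-event row is ticked at the preoperative, intraoperative and postoperative visits and dashed at the hysterectomy 1-year visit.
- **Ordinary visits, table.** In Table 1 ("Schedule of events of the CAPTURE study at baseline and scheduled visits"), adverse events are ticked at 3 to 6, 12 and 24 months.
- **Ordinary visits, text.** The section on those three visits is narrower than Table 1. Participants are evaluated "for ADRs (if medication was prescribed at the previous visit".
- **General statement.** Overall Study Design and Plan says that "both serious and nonserious adverse events (AEs) during and following procedural intervention will be reported". It names no visit and no time window.
- **Unscheduled visits.** These record why the patient came and any change to the management plan. Adverse drug reactions (ADRs) are asked about only if medication had been prescribed.

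**The concern.** Long-term safety can be described for a management option only if someone asks about harms over the long term. For hysterectomy the plan removes the visits at which Table 1 would have asked, and puts in their place one visit that does not ask. The last scheduled question about adverse events is then the one at the postoperative visit.

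A late surgical complication would reach the database only if a site reports it unprompted, if it led to an unscheduled visit whose reason is recorded, or if it shows up in the symptom item at one year. None of these routes collects adverse events systematically or grades their seriousness. The fifth objective would then rest on incomplete data for hysterectomy, whether or not any statistical test is done.

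**Working it through.** The plan gives no figure on this point to reproduce. The check is a count from the two schedules, read against the visit descriptions.

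**1. Stated schedule or omission?** Table 2 and the text on the hysterectomy visit list that visit's content separately, and both leave adverse events out. The article therefore fixes this schedule. It is neither a broken table nor a detail left to a fuller document.

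**2. Scheduled AE assessments after the postoperative visit, hysterectomy.**
Count = AE ticks in the 1-year column + AE ticks at remaining Table 1 visits = 0 + 0 = 0. The second term is 0 because the 1-year visit replaces those visits.

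**3. The same count for another procedure.** These patients keep whatever Table 1 visits remain. The count depends on when the postoperative visit falls and on which description of the ordinary visits governs.

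| Postoperative visit falls | Table 1 governs | Visit text governs, unmedicated patient |
|---|---|---|
| before the 3- to 6-month visit | 3 | 0 |
| between that visit and 12 months | 2 | 0 |
| between 12 and 24 months | 1 | 0 |

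The difference from hysterectomy is therefore 3, 2 or 1 under Table 1, and 0 for an unmedicated patient under the text. The full range is zero to three.

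**4. How much of the first postoperative year has no scheduled AE question.** The article does not say when the postoperative visit takes place. Suppose it is v months after surgery (assumption). The share of the year after that visit is (12 − v)/12:

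- v = 1: 11/12 = 92%
- v = 1.5: 10.5/12 = 88%
- v = 3: 9/12 = 75%

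**5. Effect of the fix on the count.** Ticking adverse events at the 1-year visit raises the count in step 2 from 0 to 1. No sample size or error rate changes.

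**6. What cannot be computed.** The article gives no adverse-event rates, no expected number of hysterectomies and no timing for the postoperative visit. The effect on reported AE percentages therefore cannot be derived from it.

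**The case against.** The case on the other side has four parts.

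- **Adverse events are not shut out.** The general commitment to report events following a procedure has no time limit, emergency assessments leave a record of their reason, and the 1-year visit records symptoms. This stands. A reader might infer that hysterectomy patients have no adverse-event capture at all after the postoperative visit, and the document does not support that. What is missing is a scheduled question.
- **Other patients may be no better off.** The ordinary-visit text covers only ADRs in medicated patients. The preoperative-visit text uses the same wording where Table 2 nevertheless ticks adverse events, so the AE row may mean drug reactions at non-operative visits. This also stands: it brings the lower end of the difference to zero. It does not fill the gap for hysterectomy.
- **No comparison of procedural adverse events is specified.** A reader might infer that hysterectomy will look safer in a significance test. The only safety test in Statistical Analysis concerns ADRs. Follow-up length also differs: after a hysterectomy at month 2, say, follow-up ends at month 2 + 12 = 14, against month 24 for another procedure. Some of any gap in percentages would come from that alone. The documents support neither a stated bias nor a rejection rate.
- **This is a noninterventional registry.** The objective does not demand identical ascertainment across options. That is true, but the 1-year visit is already a registry visit with its own questionnaires, and asking about adverse events there imposes no medical procedure.

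**Conclusion.** The point holds in a limited form. After hysterectomy, scheduled adverse-event assessments beyond the postoperative visit number 0, in text and table alike, and this falls short of the long-term safety objective. That conclusion needs no assumption.

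The contrast with other procedures is zero to three assessments, depending on timing and on whether Table 1 or the narrower visit text governs. The unasked share of the first postoperative year is 75% to 92% if the postoperative visit falls 1 to 3 months after surgery, which is assumed. The article does not support a claim about the size or direction of bias in AE percentages. It is a gap in data collection that is worth closing because closing it is cheap.

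**What to change.** 1. Tick adverse events in the hysterectomy 1-year column of Table 2. Add to the text on that visit the collection of all adverse events since the postoperative visit, with seriousness and relation to the procedure.
2. For 1-year visits already completed, obtain the same information by chart review where consent allows.
3. Align the text on the 3- to 6-, 12- and 24-month visits with Table 1: adverse events for all participants, and ADRs for those on medication.
4. If AE percentages are shown by management option, use a common window from treatment start (for example 1 year) or rates per person-time.

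**Cost.** One more form at a visit that already takes place, wording changes and an ethics amendment. No new visits or patients are needed. Recruitment ended in February 2018 and the last visit is expected in February 2020, so 1-year visits after the amendment can be covered prospectively and earlier ones only from charts.

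**Downside.** Patients would be asked to recall about 10 months (12 − 1.5 = 10.5, if the postoperative visit is at about 1.5 months, an assumption). Completeness would be uneven between patients reviewed from charts and those asked directly, and this should be reported.

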### Unscheduled Visits

Unscheduled visits (other than the prescribed appointments) are any unexpected visits, including emergency assessments or changes to care plans. Participants will be assessed for the reason of the visit, update and evaluation of the management plan, and ADRs (if medication was previously prescribed).

### Pregnancy Follow Up

If an unplanned pregnancy occurs with hormonal medical therapy during this study, a serious AE will be recorded. Also, the “Pregnancy follow up” form will be completed to capture baseline pregnancy information. If the patient consents to be followed up on the outcome of the pregnancy, then postdelivery follow-up information will be collected once available. No study visits will be completed during the pregnancy. Following delivery, the patient will resume the study visit schedule until completion.

### Assessment of Clinical Efficacy and Safety

This is a patient registry that tracks the routine practice and management of patients with UF in Canada. The physician will collect data at the initial and follow-up visits between 3 to 6 months, 12 months, and 24 months. Also, if a procedural intervention is performed, pre-, intra-, and postoperative data will be captured. Patients will be asked to complete the EQ-5D-5L, UFS-QOL, and the brief bleeding questionnaires as per the visit schedule outlined in Tables 1 and 2.

### Duration of Study

The duration of the study will be 2 years from the recruitment of the final patient, which occurred in February 2018. It is expected that the last visit of the final patient will occur in February 2020.

### Statistical Methods

The analysis will include all patients enrolled in the study who have been entered into the database.

### Statistical Analysis

The goal of this study is to establish a registry of Canadian patients with symptomatic UF. We have recruited a sample of 1500 patients to help describe the management of UF in this population.

Initially, exploratory data analysis will summarize all variables of interest by reporting means and standard deviations for continuous variables, and frequencies (percentages) for categorical variables. Analysis of variance will be used to compare continuous variables between treatment groups of interest. Chi-square tests will be used to compare categorical variables between the 2 groups. A linear mixed model will be employed to examine the association between treatment groups while adjusting for other covariates of clinical interest. These variables include demographics, UF history, comorbidities, medications, and medical tests (both current and previous).

The model will include a time-by-treatment-interaction term to determine whether treatments have improved quality of life relative to other treatment groups. Furthermore, a random effect will be included at the patient level to incorporate correlation arising from the repeated measures design of the study.

Since this is an observational registry, missing data and drop-outs (ie, early study termination) are expected. Statistical techniques will be used to examine the missing data (including logistic regression) and, if feasible, multiple imputations will be used to make any adjustments.

Additionally, where imputation techniques are not adequate, sensitivity analysis will be employed. All parameter estimates, confidence intervals, and *P* values will be reported from the model, and a 2-sided significance level of .05 will be used.

The original terms used by participating physicians to identify ADRs will be coded using the Medical Dictionary for Regulatory Activities (MedDRA). The MedDRA system organ class and preferred term will be used to present the number and percentage of patients with ADRs, the drug relationship, seriousness, and intensity of ADRs. Chi-square tests will be employed to compare the number of ADRs between groups of interest.

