### Participants

Approximately 1000 patients will be enrolled from 20 Canadian investigational sites, including both academic and community practices. Inclusion criteria for the study are premenopausal women at least 18 years of age with confirmed diagnosis and symptoms associated with UF that are being observed (watchful waiting), currently being treated, or initiating treatment (drug intervention, procedure intervention, or a combination of both). All patients (and the patient’s authorized legal representative) should understand the nature of the project and provide written informed consent before or at the initial study visit. Exclusion criteria for the study are known or suspected significant pelvic pathology not associated with UF and patients undergoing an emergency hysterectomy at the initial visit.

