### Potential Limitations

This registry has some limitations. The instruments used at different visits are self-reported, which may result in reporting bias. The noninterventional design can lead to selection bias as well as confounding. Finally, failure to follow up and the expected attrition of the participants at subsequent visits following recruitment could impact on the sample size, thus limiting the external validity.

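### As written, comparisons of categorical variables and adverse drug reactions between management groups are unadjusted, and the groups are not defined

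*Protocol article*

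**What the plan says.** The Statistical Analysis section starts with exploratory summaries and then gives two between-group tests. For continuous variables, "Analysis of variance will be used to compare continuous variables between treatment groups of interest". For categorical variables, "Chi-square tests will be used to compare categorical variables between the 2 groups". The two sentences describe the groups differently, and the article never says which two are meant. The Participants section admits women under watchful waiting, women already on treatment, and women "initiating treatment (drug intervention, procedure intervention, or a combination of both".

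One adjusted comparison follows: "A linear mixed model will be employed to examine the association between treatment groups while adjusting for other covariates of clinical interest". Its purpose is given next: "The model will include a time-by-treatment-interaction term to determine whether treatments have improved quality of life relative to other treatment groups". It also has a patient-level random effect.

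Logistic regression appears once, for another purpose: "Statistical techniques will be used to examine the missing data (including logistic regression".

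The section closes with safety: "Chi-square tests will be employed to compare the number of ADRs between groups of interest".

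Under Potential Limitations the article concedes: "The noninterventional design can lead to selection bias as well as confounding". The objectives at the end of the Introduction include long-term effectiveness and safety associated with the different management options.

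**The concern.** Women in this registry are not randomised to their management. A chi-square test between self-selected groups reflects who entered each group as well as what the management did. The plan deals with this for quality-of-life scores, through covariates and a random effect. It states nothing equivalent for a categorical variable or for ADRs.

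Safety by management option is a stated objective, and the ADR test is the only between-group safety comparison described. If crude P values from it were read against the .05 level, a difference in case mix could be reported as a difference between treatments.

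The undefined pair of groups adds a second difficulty. Four management options give 4 × 3 / 2 = 6 possible pairs, and the reader cannot tell which pair, or which grouping, the test concerns.

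**Working it through.** The article gives no event rates, effect size or power, so there is no figure of its own to reproduce. The check has two parts.

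**1. Which analysis the text assigns to which variable**

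| Variable | Method stated | Adjusted? | Groups named |
|---|---|---|---|
| Continuous | Analysis of variance | No | treatment groups of interest |
| Quality of life | Linear mixed model, time-by-treatment term, patient random effect | Yes | treatment groups |
| Categorical | Chi-square | No | two groups, not identified |
| ADRs | Chi-square | No | groups of interest |
| Missingness | Logistic regression | not a treatment comparison | none |

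The continuous row has an adjusted successor. The categorical and ADR rows have none.

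**2. How far a crude chi-square could mislead**

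From the document: 1500 women recruited; two-sided level .05.

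Assumed: four equal groups, so 1500 / 4 = 375 in each of the two compared; no treatment effect; one binary confounder, called severe at baseline. Its share is *a* = 50% or 60% in one group and *b* = 30% or 40% in the other. Outcome risk is *r* = 40% or 50% if severe and 20% if mild.

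Formulas:
- crude risks: p₁ = a·r + (1 − a)·0.20 and p₂ = b·r + (1 − b)·0.20
- z = (p₁ − p₂) / √(2·p̄·(1 − p̄)/375), with p̄ the mean of p₁ and p₂
- rejection rate = Φ(z − 1.96) + Φ(−z − 1.96)

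Largest case (60% v 30% severe, risk 50% v 20%):
- p₁ = 0.6 × 0.5 + 0.4 × 0.2 = 0.38
- p₂ = 0.3 × 0.5 + 0.7 × 0.2 = 0.29
- z = 0.09 / √(2 × 0.335 × 0.665 / 375) = 0.09 / 0.0345 = 2.61, so rejection is 74%

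Smallest case (50% v 40% severe, risk 40% v 20%):
- p₁ = 0.5 × 0.4 + 0.5 × 0.2 = 0.30
- p₂ = 0.4 × 0.4 + 0.6 × 0.2 = 0.28
- z = 0.02 / √(2 × 0.29 × 0.71 / 375) = 0.02 / 0.0331 = 0.60, so rejection is 9%

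All eight combinations:

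| Severe at baseline | Risk if severe 40% | Risk if severe 50% |
|---|---|---|
| 60% v 30% | 44% | 74% |
| 60% v 40% | 22% | 41% |
| 50% v 30% | 23% | 42% |
| 50% v 40% | 9% | 14% |

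**Does adjustment remove it?** A second set of assumptions was simulated, with 20,000 studies per scenario: confounder share 40% v 60% or 30% v 70%, risk 10% without the confounder and 20% or 30% with it, and 375 or 750 per group. The crude test rejected in 12% to 97% of studies. A Mantel-Haenszel test stratified on the confounder rejected in 4.8% to 5.1%. With no imbalance, the crude test also rejected in about 5%.

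**The case against.** The strongest reply is that the categorical sentence comes in a paragraph that opens with exploratory analysis. It may be meant as a crude first look, and it speaks of variables, not outcomes. An article also condenses a fuller plan, and the model for each categorical outcome is often left to the SAP. In addition, quality of life, the one outcome named for treatment comparison, is adjusted. All of this is fair, and it limits the point to what the article itself states.

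What remains is that the article fixes a test and a number of groups, and that the adjusted model it goes on to describe is linear. The ADR test stands outside the exploratory paragraph and has no adjusted successor, so it is the clearest example.

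A reader might go further and infer three things that the documents do not support:
- **That repeated visits by the same woman are pooled in a chi-square test.** No sentence says so. A test at one visit has one record per woman.
- **That four management options are collapsed into two.** No collapse is described. The wording may be a slip or may mean pairwise comparison, and the Participants section lists eligibility categories, not analysis groups.
- **That confounding by severity will occur.** The article says only that its design can lead to confounding. Treatment choice driven by severity is an assumption of the illustration.

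**Conclusion.** The point holds in a limited form. Followed as written, the plan compares categorical variables and ADRs between management groups without adjustment, and for categorical variables it does not identify the groups. This fits poorly with the objective of describing effectiveness and safety by management option and with the article's own caution about confounding. Confounding could therefore appear as a treatment difference.

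The documents support no particular size. The 9% to 74% range rests wholly on assumed group sizes, severity shares and risks; 74% is the top of that range, not a forecast. Only the qualitative result is general: when a prognostic factor is unevenly distributed, the crude test rejects too often under no treatment effect.

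This should be corrected, but it does not undermine the adjusted quality-of-life analysis. If an existing SAP already has an adjusted model for these outcomes, what remains is to define the groups and label the crude tests.

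**What to change.** - Replace the reference to two groups with the defined management groups, and use that definition for every comparison. Say where women already on treatment at entry belong. State the ADR groups separately, because the visit descriptions assess ADRs only where medication was prescribed.
- Label crude analysis-of-variance and chi-square results as descriptive.
- Analyse categorical outcomes with logistic regression, using the covariates already listed for the linear model. Where an outcome is recorded at several visits, use a logistic mixed model or GEE with a time-by-treatment term and patient-level clustering.
- For ADRs, analyse the occurrence of at least one ADR per patient in the same way, so that each woman counts once.

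The cost is a change of wording and a little more programming, with no new data. The drawback is that sparse events may not support the full covariate list, so a shorter list should be named in advance for rare outcomes.
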